The role of CAD as applied to chest x-rays is to minimize the potential errors by the interpreter and to identify potential cancerous lesions that can be missed. By improving the accuracy and consistency of radiological diagnosis, CAD will assist the radiologist in detecting early disease that can be potentially missed, allowing for early intervention and management16. We propose to use one of these systems in a screening setting. This will be the first controlled trial of chest x-ray screening in which there is a placebo control group, and the first chest x-ray screening trial that uses CAD to improve our ability to detect subtle cancers.

3.0 **OBJECTIVES**

3.1 **PRIMARY OBJECTIVE**

The primary aim of the study is to report and compare the frequency of advanced-stage lung cancers at the end of the 2 ½ year study between screened and placebo groups.

3.2 **SECONDARY OBJECTIVES**

The secondary aims are as follows:

- Determine whether lung cancer screening with chest x-rays and computer aided detection (CAD) reduces the incidence of symptomatic advanced lung cancer compared to no screening in a high-risk population. The presence of advanced symptomatic lung cancer will be determined by the Outcomes Review Committee.
- Compare the disease-specific mortality between screening with chest x-ray and CAD versus no screening. This is the endpoint used in many RCTs of lung cancer screening; thus, we will be able to compare our study results to the results of these other trials.
- Compare the all-cause mortality rate between screening with chest x-ray and CAD versus no screening. This endpoint includes all deaths including those attributed directly and indirectly to screening.
- Compare the length of time between randomization and the incidence of symptomatic advanced lung cancer for screened subjects versus controls. This analysis will provide data about how screening might delay the development of advanced lung cancer.
- Measure the monetary cost relative to the quality of life between screening with chest x-ray and CAD versus no screening. The comparison of quality of life since randomization between the two study arms will reveal differences over time due to screening. Coupled with an assessment of monetary costs, cost-utility of screening will be measured. Note that the cost-utility analysis will be performed on a subset of the study participants.

4.0 **SELECTION OF PATIENTS**

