A 4-variable stratified randomization design will be applied based on the following stratification variables: site of enrollment (main campus, east, west, or south), age (<65 –versus- >65 years of age), gender, and symptoms status (no reported chronic cough or shortness of breath -versus- reported chronic cough or shortness of breath). A blocked stratified randomization scheme will be used. There will be 8 strata within each enrollment site: 2 ages x 2 genders x 2 symptom statuses (total of 32 strata). Within each stratum we will use a randomized block size of variable size for that stratum.

7.0 **TECHNICAL DESCRIPTION OF CHEST X-RAY**

Patients selected to undergo a chest x-ray will be subjected to the standard procedure in which a frontal view would be obtained. The test will be performed at different locations using digital equipment that is available throughout the Cleveland Clinic Health System (CCHS).

The standard technical factors will be:

PA View

125kVp

1.60mAs

500ms

Left and right AEC sensors

72” SID

The radiation dose to the patient is 20 millirems for the frontal view (PA). That is less than a 6% of the yearly radiation dose that every person is exposed from normal background radiation (360 millirems). It should also be noted that the radiation generated by the chest x-ray procedure is limited to the chest organs while the background radiation affects the whole body.

Patients that will be selected to be in the control group will be introduced to a chest x-ray room and be placed against the x-ray unit however no exposure will be triggered and no image will be obtained. There will be no radiation exposure to the patient.

8.0 **INTERPRETATION OF CHEST X-RAY AND CAD**

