The primary outcome measure is the frequency of advanced-stage cancers detected during the course of the 2 ½ year study. These advanced-stage cancers may be detected during the study's planned screenings, through progression of preclinical disease to clinical symptomatic disease, and, less frequently, during medical testing/screening for other purposes (e.g. presurgical work-up). Advanced-stage cancers will be defined as stage III or IV cancers and will be assessed as clinically indicated, which usually includes PET imaging, additional invasive testing (i.e. tissue sampling), and sometimes brain imaging.

12.2 **SECONDARY ENDPOINT ASSESSMENT**

A secondary endpoint is the presence/absence of symptomatic lung cancer. To assess this outcome, an expert outcome review committee, consisting of a pulmonologist and an oncologist, will be convened at the end of the study (after March 2011). The committee members, each working independently, will review all cases of diagnosed, pathology-proven lung cancer as well as all deaths. Committee members will be blinded to the randomization assignment of the subjects and results of screening tests. Based on the subject’s self-reported symptoms assessment during the study and their medical records, and death certificates (if appropriate and available) the committee members will determine whether the subject is asymptomatic or has symptoms that correlate with their diagnosis of lung cancer. Subjects determined to have symptoms of lung cancer by both committee members will be classified as events for calculation of this secondary endpoint. In cases where the two committee members disagree, the committee members will meet to discuss the cases and reach consensus. Deaths due to lung cancer and deaths due to the management or treatment of diagnosed lung cancer will also be classified as events. For all events, committee members will decide on, to within 6 months, the time at which the subject developed symptoms.

Note that for the assessment of the primary and secondary endpoints, subjects who are determined to have lung cancer that has metastasized will be considered a censored event at the time of diagnosis. These subjects’ lung cancer will not be classified as events in the assessment of the primary and secondary endpoints.

Definition of "Advanced Symptomatic Disease":

The following criteria will be assessed by the Outcomes Review. All three criteria must hold.

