1. The patient has been diagnosed with non-small cell carcinoma, stage II or

higher, or small cell carcinoma, any stage.

2. The patient has experienced a symptom that led them to seek contact with a

physician since the time of the last study visit; or at the time of their next study

visit, the patient has developed a new symptom or a change in a chronic

symptom within the past 6 weeks, that did not yet lead to a doctor's visit.

3. The symptom(s) described in #2 are felt to be related to the diagnosis of lung

cancer as adjudicated by the Outcomes Review Committee.

For the other secondary endpoints, the committee will review the medical records and self-reported symptoms assessment of all deaths and determine if the death is due to lung cancer.

13.0 **STATISTICAL ANALYSIS PLAN**

13.1 **PRIMARY AIMS:**

Analyses will be based on an intent-to-treat perspective. We will test the null hypothesis that at the time of diagnosis the frequency of advanced-stage cancers is the same for screened and unscreened groups; the alternative hypothesis is that the frequency of advanced-stage cancers is different for screened and unscreened groups. These hypotheses will be tested at the end of the two and a half-year study, i.e. after March 31, 2011. The frequency of advanced-stage cancers in the two study arms will be compared using logistic regression analysis. A model will be fit to describe the probability of advanced-stage cancer as a function of the following independent variables: age, gender, symptoms status at the time of enrollment into the study (i.e. symptoms present or not present), study arm, and two-way interactions with study arm. The fit of the model will be assessed using the Hosmer-Lemeshaw goodness of fit test. The coefficients for study arm and interactions with study arm will be assessed, after adjusting for other covariates, using a likelihood ratio test with significance level of 0.05 (two-tailed).

13.2 **SECONDARY AIMS:**

One of the secondary aims of the study is to determine whether lung cancer screening using chest x-rays and CAD reduces the incidence of symptomatic advanced lung cancer relative to no screening. The observed cumulative incidence of symptomatic advanced lung cancer, measured in events per person per years observed, will be compared between the two study arms. The analysis will be carried out from an intent-to-treat perspective.

The incidence rate of symptomatic lung cancer will be estimated as follows

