Incidence rate at time *t*= [# events by *t*] / [# of person-years at risk until *t*].

where “event” is the development of symptoms due to lung cancer or death due to treatment for the disease or lung cancer death (whichever is observed first). These events will be determined by the outcome review committee at the end of the study (after March 2011). The number of person-years at risk is equal to t – e, where t is the smaller of [time at which the subject experienced symptoms of lung cancer, time at which the subject was lost to follow-up if the subject did not die from lung cancer or from its treatment before *t*, time at which the subject died from lung cancer or its treatment, *t*], and

e is the number of study months before the subject was enrolled into the study (i.e. e=0 at the start of the study).

The following null hypothesis will be tested: the incidence rates of the screened and control subjects are equal. The alternative hypothesis is the incidence rates of the screened and control subjects are not equal. A stratified analysis will be used. There will be four strata:

- age < 65 years at enrollment; none/mild pulmonary symptoms at enrollment
- age > 65 years at enrollment; none/mild pulmonary symptoms at enrollment
- age < 65 years at enrollment; moderate pulmonary symptoms at enrollment
- age > 65 years at enrollment; moderate pulmonary symptoms at enrollment.

Note that only four strata were chosen because the overall number of events will be small. These particular four strata were chosen because we expect that age and pulmonary health at enrollment are the strongest predictors of the development of lung cancer and curability of lung cancer.

For each stratum i, the data can be summarized as follows:

Screened Control Total

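### The event analyzed for symptomatic advanced lung cancer (13.2) omits the stage/histology condition in that endpoint's own definition (12.2)

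*Protocol*

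**What the plan says.** **Aim.** Protocol 3.2 asks whether screening "reduces the incidence of symptomatic advanced lung cancer compared to no screening in a high-risk population". Section 13.2 restates the target: "The observed cumulative incidence of symptomatic advanced lung cancer" is to be compared between arms. A further aim in 3.2 is the time from randomization to that same outcome.

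**Definition.** The last part of 12.2 defines *Advanced Symptomatic Disease* and says "All three criteria must hold". Criterion 1 begins "The patient has been diagnosed with non-small cell carcinoma, stage II or"; it continues to higher stages and adds small cell cancer at any stage. Criteria 2 and 3 require a symptom and the committee's judgment that it is related to the lung cancer.

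**Event rule for the committee.** Section 12.2 opens differently: "A secondary endpoint is the presence/absence of symptomatic lung cancer". A subject whom both members judge to have symptoms of lung cancer is an event. Deaths from lung cancer, or from its management or treatment, are added. Stage is not mentioned.

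**Analysis.** In 13.2 the rate is headed as that of symptomatic lung cancer, and the event "is the development of symptoms due to lung cancer or death due to treatment for the disease or lung cancer death". Person-time stops at the first lung cancer symptom. The Cox model uses time to symptomatic disease. The paragraph after the confidence interval formulas nevertheless calls the analysis one of symptomatic advanced disease.

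**The concern.** One endpoint has two event definitions, and the formula uses the one that does not match the aim. Criterion 1 is the only part of the definition that makes the disease advanced. Without it, the Mantel-Haenszel ratio compares the arms on all symptomatic lung cancer plus deaths, and would be reported under the advanced label.

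This matters most in a screening trial, where the question is whether disease is caught before it becomes advanced. A symptomatic stage I cancer is not the outcome the aim describes. If the choice is left open until the committee has reviewed the cases, the definition could be settled after the cases are known.

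**Working it through.** No figure in the protocol bears on this endpoint: there is no expected rate ratio, event count or power for it. The check is a comparison of the rules, case by case.

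| Case | Three criteria (12.2) | Committee event rule (12.2) | Event in 13.2 |
|---|---|---|---|
| Symptomatic non-small cell, stage II or above* | event | event | event |
| Symptomatic small cell, any stage* | event | event | event |
| Symptomatic non-small cell, stage I | **not an event** | **event** | **event** |
| Asymptomatic screen-detected stage I, alive, no later symptoms | not an event | not an event | not an event |
| Death from lung cancer or its treatment | not addressed by the criteria | event | event |

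*Apart from metastasized cases, discussed below.

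1. Row 3 is the contradiction. The committee rule and the 13.2 event agree with each other; both disagree with the definition and with the aim.
2. The denominator follows the same stage-free rule. If only the numerator were corrected, a subject with a symptomatic stage I cancer would stop contributing person-time without having had an event. Both must change together.
3. The Cox endpoint has the same omission, measured against the time-to-event aim in 3.2.
4. Effect on the estimate. Let q be the share of placebo-arm symptomatic events that are stage I non-small cell, RR_adv the rate ratio for events meeting criterion 1, and RR_I the rate ratio for symptomatic stage I non-small cell cancer. Treat person-years as practically equal under both rules, since events are few, and leave deaths aside. Then

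 RR_13.2 = (1 − q) × RR_adv + q × RR_I,

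 so RR_13.2 − RR_adv = q × (RR_I − RR_adv). This is zero only if q = 0 or the two ratios are equal. Its sign is the sign of RR_I − RR_adv.
5. The protocol supplies none of q, RR_adv or RR_I for the stage II-or-above definition. Assumed values, chosen only to show that either direction is possible, with q from 5% to 30%:
 - RR_adv = 0.65, RR_I = 1.0: 0.95 × 0.65 + 0.05 × 1.0 = 0.668, up to 0.70 × 0.65 + 0.30 × 1.0 = 0.755 (toward 1).
 - RR_adv = 1.0, RR_I = 0.65: 0.95 × 1.0 + 0.05 × 0.65 = 0.983, down to 0.70 × 1.0 + 0.30 × 0.65 = 0.895 (away from 1).
6. Metastasized disease. A note in 12.2 censors these cases at diagnosis and excludes them as events for the primary and secondary endpoints. Criterion 1 has no upper stage limit, and lung cancer deaths count as events. Any single event definition must settle this as well.

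**The case against.** **The stage test is implied.** Section 13.2 leaves events to the outcome review committee, 3.2 says that committee determines advanced symptomatic cancer, and the label after the formulas is the advanced one. Shorthand is therefore a possible reading. It does not hold, because 12.2 tells the committee to classify events for this endpoint on symptoms alone, and 13.2 then spells out the event without stage.

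**Symptomatic simply means advanced.** The placebo-arm formulas in section 14 have no stage term. If that were the intent for this endpoint, the stage limit in criterion 1 would do no work.

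**Two endpoints were meant.** Section 3.2 has no aim for symptomatic cancer of any stage. On this reading the endpoint it does list would have no analysis.

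A reader might also infer more than the documents support:

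- *That committee events and analyzed events differ.* They follow the same rule; the conflict is with the three criteria and the aim.
- *That treatment deaths after stage I disease are misclassified, mainly in the screened arm.* Both 12.2 and 13.2 add such deaths as events, and the fix keeps them. An asymptomatic screen-detected stage I cancer is not an event under either rule unless symptoms or such a death follow.
- *That the number of affected events can be read from section 14.* Its placebo formulas at N = 4000 give 14.4 + 25.9 + 7.1 = 47.4 (Table 2: 47.5), but that count is labeled symptomatic and advanced-stage, and 12.1 defines advanced-stage as III or IV. A stage I share cannot be taken out of it, and no share is given.
- *That the sign or significance of the rate ratio would change.* No calculation from the documents shows this.
- *That stage II or above here contradicts stage III/IV in 12.1.* These are separately defined terms for different endpoints, and neither needs to be a subset of the other.
- *That the analysis strata are wrong.* Section 13.2 uses categories such as "moderate pulmonary symptoms at enrollment", while randomization in 6.0 uses "no reported chronic cough or shortness of breath -versus- reported chronic cough or shortness of breath". Analysis strata need not equal randomization strata, 13.2 gives reasons for its choice, and graded respiratory questionnaires are collected at baseline.

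**Conclusion.** The contradiction stands and is confined to one class of case: symptomatic stage I non-small cell cancer is an event under the committee rule and the 13.2 analysis, but not under the definition of the endpoint. As written, the Mantel-Haenszel ratio and the Cox model would not estimate the effect on symptomatic advanced lung cancer.

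The size and direction of the resulting difference cannot be determined from the documents; the ratios in the working are assumptions, not estimates. The primary analysis and the two mortality comparisons do not use this event and are unaffected by the omission. The text is wrong as written and should be corrected. The endpoint is secondary, though it is the first listed.

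**What to change.** Before the outcome review committee begins adjudication (12.2 convenes it after March 2011):

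- State one event in both 12.2 and 13.2: the earlier of (a) the date on which all three 12.2 criteria are met and (b) death from lung cancer or its treatment. Present deaths as an explicit alternative to the three criteria.
- Replace the stage-free committee rule in 12.2, and have the committee date the event on this definition.
- Use that event in the numerator, the person-time, the Mantel-Haenszel ratio and the Cox model, under one label.
- If symptomatic lung cancer of any stage is also of interest, report it as a separately labeled analysis.
- Reconcile the event with the 12.2 note on metastasized lung cancer, so that it is clear whether such cases, and later deaths among them, count.

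The cost is a wording amendment to 12.2 and 13.2. No new data are needed: the committee reviews pathology-proven cases, and section 10 already collects diagnosis, pathology staging and mortality for every subject diagnosed with lung cancer. Criterion 1's stage threshold and the four analysis strata need no change on this account.

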# events a1i a0i Mi

Person-years N1i N0i Ti

______________________________________________________________________________

The Mantel-Haenszel rate ratio19 is given by

RR=[a1iN0i/Ti] / [a0iN1i/Ti].

The variance of the ln(RR) is given by20

Var[ln(RR)] = [MiN1iN0i/Ti2] / [(a1iN0i/Ti)(a0iN1i/Ti)].

The 95% CI for RR is as follows:

lower = exp[ln(RR) – zval * Var(ln(RR))1/2

upper = exp[ln(RR) + zval * Var(ln(RR))1/2,

where zval is the value from the standard normal distribution whose value will depend on the time of the analysis (see subsection on Interim Analyses).

If the 95% CI for RR does not include the value one, then we will reject the null hypothesis.

The analyses described above for the cumulative incidence of symptomatic advanced disease will also be performed for disease-specific mortality and all-cause mortality.

A Cox proportional hazards model will be fit to compare the two study arms on the time from randomization until symptomatic disease. Covariates will be included in the model, such as age, gender, race, smoking history, symptoms at presentation, as well as site of enrollment. A significance level of 0.05 will be applied.

13.3 **OTHER ANALYSES:**

In the intervention arm, for each screening, we will report the number of subjects with actionable findings and the type of findings. We will report the follow-up results of these findings. This will provide data on the false positive rate and the size and stage of detected cancerous nodules.

We will test the effect of CAD on radiologist performance. This will include the effect of CAD on the radiologists’ sensitivity, as well as the effect on the false positive rate. First, we will separate the screened cases into one of three groups based on follow-up results, as available: cancerous nodule(s) present, benign nodule(s) present and no cancerous nodules present, no nodules present. For each group we will compare the frequency with which radiologists reported an actionable nodule without CAD versus with CAD. For each group the frequencies will be compared using a McNemar’s test, modified for clustered data.21  The modification is necessary because two radiologists will be interpreting each case. A significance level of 0.05 will be applied.

14.0 **SAMPLE SIZE CONSIDERATIONS**

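### The person-time rule in section 13.2 does not stop at death from other causes, lets censoring depend on later lung-cancer death, and is reused for mortality with its stop at symptom onset; the effect is small

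*Protocol*

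**What the plan says.** Section 13.2 divides the number of events up to the analysis time t by the person-years at risk up to t. An event "is the development of symptoms due to lung cancer or death due to treatment for the disease or lung cancer death", whichever is seen first. "The number of person-years at risk is equal to" t minus e, where the end point is the smallest of four times:

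- the onset of lung-cancer symptoms
- loss, but only on a condition that looks ahead to the analysis time: "time at which the subject was lost to follow-up if the subject did not die from lung cancer". The same condition covers deaths that treatment caused.
- death, but of one kind only: "time at which the subject died from lung cancer or its treatment"
- the analysis time itself.

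The entry offset is in months: "e is the number of study months before the subject was enrolled into the study".

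After the Mantel-Haenszel rate ratio, its variance and its confidence interval, the section says that the analyses "will also be performed for disease-specific mortality and all-cause mortality". It gives no separate event or stop time for either. Section 3.2 makes clear that all-cause mortality takes in every death. Section 12.2 has the outcome committee review all deaths, with death certificates where they can be had. It also says that subjects whose lung cancer has metastasized are censored at diagnosis and are not events.

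**The concern.** A person-time denominator should cover the time during which a subject is alive, under observation and able to have the event. The written rule departs from this in three ways.

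1. Death from another cause does not end the clock. For symptomatic cancer this adds time when no event is possible. For all-cause mortality the clock does not stop at the event being counted.
2. Loss to follow-up ends time for most lost subjects, but not for those later known to have died of lung cancer. Time and events after loss enter the rate only for subjects who have the event, so censoring is decided by a future outcome.
3. Carried over to mortality, the rule still stops at symptom onset, which usually precedes lung-cancer death.

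At stake are the reported incidence and mortality rates. Section 3.2 includes disease-specific mortality so that results can be set beside those of other screening trials, and that needs a sound denominator.

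**Working it through.** The protocol states no event count, rate or power for these person-time endpoints, so there is no figure of its own to reproduce.

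**Single subjects under the written rule** (t = 30 months, e = 0)

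| Subject | Time at risk as written | Consequence |
|---|---|---|
| Dies of another cause at month 10, not recorded as lost | min(30) = 30 months | 30 - 10 = 20 months counted after death |
| Lost at month 10, no lung-cancer death | min(10, 30) = 10 months | censored at loss |
| Lost at month 10, lung-cancer death at month 24, no symptom date | min(24, 30) = 24 months, with event | loss ignored because of a later outcome |
| Symptoms at month 8, lung-cancer death at month 24 | min(8, 24, 30) = 8 months | for mortality, the clock stops 24 - 8 = 16 months before the death |

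**Size, by simulation of the written rule against ordinary person-time.** Ordinary person-time stops at the endpoint's own event, any death, loss or t.

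- From the protocol: 10% yearly loss, 12-month entry period and 4,000 per arm (section 14.0); 30-month study.
- Assumed, not in the protocol: symptomatic cancer 0.6% per year; mean 12 months from symptoms to lung-cancer death; other-cause death 0.5%, 1% or 2% per year; 0%, 50% or 100% of lung-cancer deaths after loss becoming known, with the symptom date then also known; other-cause deaths after loss not counted.
- Lung-cancer deaths after symptom onset are counted, because the numerator is events up to t.

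Person-years per 4,000 subjects, symptomatic endpoint (no later deaths known):

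| Other-cause death per year | As written | Ordinary | Excess |
|---|---|---|---|
| 0.5% | 7161 | 7123 | +0.53% |
| 1% | 7163 | 7088 | +1.06% |
| 2% | 7167 | 7017 | +2.13% |

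Rate as written divided by ordinary rate, for 0% / 50% / 100% of lung-cancer deaths after loss becoming known:

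| Other-cause death per year | Symptomatic cancer | Lung-cancer mortality | All-cause mortality |
|---|---|---|---|
| 0.5% | 0.995 / 1.019 / 1.043 | 0.998 / 1.068 / 1.139 | 0.998 / 1.026 / 1.054 |
| 1% | 0.990 / 1.013 / 1.039 | 0.993 / 1.062 / 1.134 | 0.993 / 1.010 / 1.028 |
| 2% | 0.979 / 1.003 / 1.026 | 0.982 / 1.051 / 1.120 | 0.982 / 0.992 / 1.002 |

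The lower end is purely the denominator: when no later death is known, the same deaths are counted under both rules. At 2% other-cause death the mortality ratio is 7040 / 7167 = 0.982. The upper end comes from the conditional loss rule, which adds lung-cancer deaths after loss with almost no matching time from other lost subjects.

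**Between-arm ratio.** With a true ratio of 0.65 for symptomatic cancer and the same loss and ascertainment in both arms, the rate ratio under the written rule differs from the ordinary one by about 0.01 or less on all three endpoints.

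**The case against.** The best defence is that the intent is clear. The sentence on mortality most naturally carries over the method (strata, Mantel-Haenszel ratio, interval); the event has to be swapped, and a sensible analyst would swap the stop time with it. The clause on loss can be read as saying that a subject whose lung-cancer death is known is not lost, which suits an intent-to-treat analysis with few events. Death from another cause can be treated as an exit like loss.

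Part of this stands. The substitution is probably intended, and using known deaths is legitimate. But the rule is a closed list and says none of it. Treating other-cause death as loss fails for all-cause mortality, where that death is the event. Using deaths after loss is sound only if all lost subjects are traced alike and their time after loss is counted too, and the rule does the opposite.

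A reader might also infer three stronger things, none of which the protocol supports:

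- That disease-specific mortality loses most of its events. The numerator is all events up to the analysis time, so deaths after symptom onset still count; only the denominator is cut short.
- That all-cause mortality is understated. The direction depends on how many deaths after loss become known, and the ratio runs either side of 1.
- That the month-based offset is an error in the rates. The denominator is labelled person-years, so this is a unit conversion, and it cancels in the rate ratio.

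**Conclusion.** The rule is wrong as written, and the effect is small. It is stated in the protocol's own analysis section, so it is not a detail left for later. Absolute rates are misstated by about -2% to +4% for symptomatic cancer, -2% to +14% for lung-cancer mortality and -2% to +5% for all-cause mortality, with the sign set mainly by how many deaths after loss become known. These ranges rest on assumed cancer, fatality and other-cause death rates and would shift with others.

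The test of each null hypothesis uses the interval for the rate ratio, which moves by about 0.01 or less, so no conclusion about screening is likely to turn on this. That holds while loss and the tracing of later deaths are the same in both arms; if they differ, the conditional loss rule could move the ratio further. This is a worthwhile correction, not a threat to the trial.

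**What to change.** Replace the person-time sentence in section 13.2 with a definition for each endpoint:

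- Person-time, in years, ends at the earliest of that endpoint's own event, death from any cause, loss to follow-up and the analysis time.
- For disease-specific and all-cause mortality it does not stop at symptom onset.
- Loss is handled the same way whatever happens later: either censor everyone at loss, or count deaths and person-time after loss for everyone, using the same vital-status ascertainment in both arms.

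Then reconcile this with section 12.2, which censors metastasized lung cancer at diagnosis for the primary and secondary endpoints; state whether and how that applies to each person-time endpoint.

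The cost is a few rewritten lines. Censoring everyone at loss needs no new data; the alternative needs a vital-status search of all lost subjects.
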